#### Fatigue

The Fatigue Severity Scale (FSS) is a self-reported scale and has been used previously in prostate cancer patients treated with ADT [21] and in patients with advanced stage cancer of the prostate [22]. Patients are asked to report their degree of agreement (on a seven-point scale) with nine items related to fatigue. Therefore, scores can range between 9 (indicating minimum fatigue) and 63 (indicating maximum fatigue). The validity of this scale is supported by its good correlation with both the EORTC Fatigue scale (Spearman Rank Correlation Coefficient r = 0.83) and the bi-dimensional fatigue scale (r = 0.62). A previous study of cancer related fatigue reported that 95% of an elderly control population without cancer scored less than 42 on the FSS scale [22]. Therefore, in this study 'severe fatigue' for cancer patients was defined as a score of 42 or greater based on the results of a study by Stone et al in prostate cancer patients treated with ADT [21].

#### Quality of life

The Functional Assessment of Cancer Therapy-Prostate (FACT-P) is used to assess prostate cancer related quality of life [23]. The FACT-P is a 40-item self-reported questionnaire assessing a range of quality of life domains: physical, social/family, emotional, and functional well being. In addition, a 12-item prostate cancer subscale (PSC) which is specific to the symptoms and side effects associated with prostate cancer treatment such as body image, pain, urinary and sexual functioning is also used. Responses to questions use a five-point Likert-type scale ranging from 0 (not at all) to 4 (very much). The scores are summed to produce a subscale score for each domain assessed. The subscale scores range from 0 to 28 for the physical, social/family, and functional well being scales, 0 to 24 for the emotional well being scale, and 0 to 48 for the PSC, and higher scores represent better quality of life. The scores of these four domains are summed to calculate the FACT-G (Functional Assessment of Cancer Therapy-General) and total scores of FACT-G and PSC are added up to produce a FACT-P score. An additional score, the Trial Outcome Index (TOI) is created by summing the physical well-being, functional well-being and PCS scores. This instrument has been used previously in prostate cancer patients receiving ADT [24]. It has been considered a reliable instrument with sensitivity to change in prostate specific antigen (PSA) scores and performance status [23].

### Secondary outcomes

Secondary outcomes include nutrient intake, physical activity and perceived stress.

#### Nutrient intake

To reduce the possibility of memory recall problems for this older patient group a 7-day food diary (7DD) is used to assess food and nutrient intake. The patients are asked to record, in as much detail as possible, all food and beverages consumed over a 7-day period. The food diary contains instructions for completion, one page to record foods and drinks eaten during seven time points (before breakfast, breakfast, before lunch, lunch, before dinner, dinner, after dinner) and alcohol over a 7 day period. The instructions included the provision of typical portion sizes to help the patients to indicate the amount of each food consumed. Patients are also encouraged to describe the portion size consumed using other measures if they wish, such as weight in grams or ounces, or in household units, such as tablespoons, cups, slices etc. At the time of the patients' visit the trained nutritionist clarified any omissions and collected additional information if required such as the cooking methods used, brands of foods consumed and portion sizes if these were unclear. The 7DD has been used in the UK EPIC (European Prospective Investigation of Cancer and Nutrition) study [25] amongst others and is a manageable method for our population. It has been demonstrated that a 7DD provides a better estimate of average intake than a food frequency questionnaire or a 24 hour-recall [25,26]. A computer based software programme (WISP) will be used to interpret the food intake data to provide nutrient and food group intake estimates. The total number of servings of fruit and vegetable consumed will be calculated using the Food Standard Agency guidelines [19].

A fasting blood sample is collected for analysis of serum ferritin, antioxidant vitamins, dietary lipids (total cholesterol, high-density lipoprotein, low-density lipoprotein, triglycerides), C-reactive protein and albumin. A total of 30 ml of blood is collected and following appropriate processing for serum and plasma are stored in -80°C freezer.

#### Physical activity

Physical activity is assessed with 7-Day Physical Activity Recall (7-DPARQ) [27,28]. This is an interviewer-administered measure assessing current and recent past physical activity from the last 7 days. Information on moderate, hard and very hard activities and time spent sleeping is gathered from the interview and light activities is imputed from the time remaining. Additionally, patients report how typical the week's activity is compared to their activity in the previous three months. The 7-DPARQ measures energy expenditure and yields a summery score in kcal/kg^-1^/day^-1 ^for the previous week. It has been validated and used for prostate cancer patients in previous studies [12,29].

Functional capacity is measured using a 6-min Walk Test [30,31], which was used in previous studies of prostate cancer patients [9,29]. This test includes a measure of the distance walked, to the nearest metre in 6 minutes. This functional measure was chosen rather than a measure of physiological fitness as it appears to be a more suitable outcome for an elderly population [29]. The 6-min walk test has a high test-retest reliability over a 2-week time frame (*r *= 0.87) [32].

#### Stress

Psychological stress is assessed using the Perceived Stress Scale (PSS-10), which is the most widely used psychological instrument for measuring the perception of stress among prostate cancer survivors [33-35]. The PSS-10 is a 10-item questionnaire designed to measure the perceived stress and the degree to which patients found their lives unpredictable, uncontrollable, or overloaded in last 1 month. Questions are rated on a 4-point Likert scale with responses ranging from 0 = "never" to 4 = "very often." [36]

#### Other assessments

The transtheoretical model (TTM) is used to assess a patients' readiness to change their lifestyle behaviour [37]. Patients will be categorised according to their stage of readiness to change and this information will be taken into consideration in the analysis and interpretation of the impact of the intervention. Patients are asked, 'on average do you - eat at least 5 servings of vegetables and fruits each day; avoid eating too much fat; walk 30 minutes every day at a brisk pace, 3 to 5 times/week?'. Responses include: Yes - 'more than six months' (interpreted as maintenance), 'less than six months' (interpreted as action); No - 'intend to in the next 30 days' (interpreted as preparation), 'intend to in the next 6 months' (interpreted as contemplation) and not intending to in the next 6 months (interpreted as pre-contemplation). Stage of readiness to change is also considered in the delivery of the intervention. For example, the potential benefit of a dietary and physical activity intervention is really emphasised to those men who are in a stage of contemplation/precontemplation with respect to making diet and physical activity changes.

A structured questionnaire is used to collect information on age, socioeconomic status, education, family and social support, tobacco and alcohol intake, barriers to exercise and diet, supplementation use and family history of prostate cancer. A clinical history, including the date of diagnosis, stage of disease and treatment details is recorded from the patient's medical notes during screening. Data related to adverse events are collected continuously via follow-up phone call.

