**Methods:**

Men are recruited to this study if their treatment plan is to receive ADT for at least 6 months. Men who are randomised to the intervention arm receive a home-based tailored intervention to meet the following guidelines a) ≥ 5 servings vegetables and fruits/day; b) 30%-35% of total energy from fat, and < 10% energy from saturated fat/day; c) 10% of energy from polyunsaturated fat/day; d) limited consumption of processed meats; e) 25-35 gm of fibre/day; f) alcoholic drinks ≤ 28 units/week; g) limited intake of foods high in salt and/or sugar. They are also encouraged to include at least 30 minutes of brisk walking, 5 or more days per week. The primary outcomes are change in body composition, fatigue and quality of life scores. Secondary outcomes include dietary intake, physical activity and perceived stress. Baseline information collected includes: socio-economic status, treatment duration, perceived social support and health status, family history of cancer, co-morbidities, medication and supplement use, barriers to change, and readiness to change their health behaviour. Data for the primary and secondary outcomes will be collected at baseline, 3 and 6 months from 47 intervention and 47 control patients.

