A diet and physical activity intervention that could address some of these side effects could be beneficial to prostate cancer patients treated with ADT. Experimental studies examining the role of exercise during ADT treatment for prostate cancer have shown that 10-20 weeks of exercise is an effective way to reduce fatigue and depression, improve quality of life, increase muscular fitness and strength [8-11], and improve physical functional capacity preventing adverse effects on body composition [9]. Indeed 20 weeks of exercise has been shown to preserve lean body mass and prevent an increase in fat mass [11]. Changes in dietary intake at the time of treatment may also help to counteract the changes in body composition associated with ADT. Several randomised controlled trials (RCTs) of diet and physical activity interventions in prostate cancer patients have begun in recent years and include the FRESH START trial, Project LEAD, and RENEW. However the men recruited within these studies have received all types of treatment modalities [12-14]. Therefore, the impact of a diet and physical activity intervention on the side-effects related to ADT, a group that experiences major changes in body composition, has not yet been discussed in any of these studies.

To date very little information is known about dietary intake and physical activity levels of prostate cancer patients in the UK. In general however, cancer patients are highly motivated to seek information about food choices, physical activity, dietary supplement use, and complementary nutritional therapies in an attempt to improve their response to treatment, speed-up recovery rates, reduce the risk of cancer recurrence, and/or to improve their quality of life [15]. The American Cancer Society has recently published nutrition and lifestyle guidelines for cancer survivors [16] although the impact of these guidelines on outcomes relevant to prostate cancer patients treated with ADT are unknown. In addition, for long-term prostate cancer survivors, an appropriate weight, a healthy diet, and a physically active lifestyle aimed at preventing recurrence, second primary cancers, and other chronic diseases should be a priority. Therefore, we have developed an intervention aimed at encouraging patients treated with ADT to meet healthy eating guidelines and achieve at least 30 minutes of brisk walking at least 5 days per week to reduce treatment related side-effects and improve overall quality of life.

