#### Moderate physical activity

Brisk walking at least 30 min per day, in addition to usual activities on 5 or more days of the week.

The diet and physical activity intervention is tailored to each patient based on the information collected during their baseline interview. The nutritionist meets each patient to discuss their calculated energy and nutrient requirements. Dietary recommendations are based on the information collected on weight, physical activity levels and baseline dietary intake. Energy is calculated based on actual body weight; however, 500 kcal/day reduction is advised to the overweight/obese patients to prevent or reduce weight gain. Each patient in the intervention arm receives an individualised guidebook with tips and guidelines to help adherence to the diet. The guidebook includes; a sample menu to provide an example of the amounts and type of foods that can be included for breakfast, lunch, dinner and snacks; a list of portion sizes for foods typically eaten; tips to incorporate more fruit, vegetables and fibre, and reduce total fat, saturated fat, sugar and salt; a list of healthier foods choices and a list of foods that should be chosen less frequently from all food groups; examples of healthy alternative menus for breakfast, snacks, lunch and dinner.

The physical activity intervention is also tailored to each patient based on their baseline physical activity level. As a minimum, each patient is asked to walk at a brisk pace for at least 30 minutes per day, 5 times or more per week. However, men who are already physically active are advised to increase the duration and frequency of walking each week. They are also asked to set a goal of increasing the number of steps by at least 10% every week. A pedometer is provided to each participant in an effort to encourage them to comply with the physical activity intervention and as an independent measure of physical activity levels during the intervention period.

Men in the control group will receive standard care during the intervention period but will be offered the same guidelines at the end of the 6 month intervention.

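### The readiness-to-change item for walking is ambiguous, and on no reading does its criterion match the trial's walking target of 5 or more days a week, so men can be misstaged for walking

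*Protocol article*

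**What the plan says.** Under Other assessments, the protocol article sets out the question used to stage patients on the transtheoretical model. Its walking part asks whether the man does, on average, "walk 30 minutes every day at a brisk pace, 3 to 5 times/week". A yes is split by duration: over six months is maintenance, under six months is action. A no is split by intention into preparation, contemplation or pre-contemplation.

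The walking target appears four times elsewhere, always with the same threshold:

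- Abstract, Methods: "at least 30 minutes of brisk walking, 5 or more days per week".
- Background: "achieve at least 30 minutes of brisk walking at least 5 days per week".
- Moderate physical activity, opening statement: "Brisk walking at least 30 min per day, in addition to usual activities on 5 or more days of the week".
- Moderate physical activity, minimum for every intervention patient: "each patient is asked to walk at a brisk pace for at least 30 minutes per day, 5 times or more per week".

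The stage has three stated uses. Measuring it is one of the Specific objectives. Other assessments says that it will inform the analysis and interpretation of the intervention's impact. The same section adds: "Stage of readiness to change is also considered in the delivery of the intervention". The example given is stronger emphasis on the potential benefit for men in contemplation or pre-contemplation. Table 1 schedules the instrument at baseline only.

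**The concern.** A stage of readiness has meaning only relative to a defined behaviour. Here the behaviour in the item is not the behaviour the trial asks for, and the item's own two frequencies leave each man to decide which one he is answering. A yes does not establish that he is at the trial's target, and a no does not establish that he is below it.

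What is at stake is the description of readiness for walking, which is the whole physical activity component, and any later statement about whether men at different stages responded differently. Such a statement would mix men at target with men below it inside the same stage. Because the instrument is not repeated, no later readiness measurement can correct a wrong baseline stage.

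**Working it through.** The article gives no figure to reproduce, so the check sets the thresholds side by side and classifies each walking frequency under each possible reading of the item.

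**Inputs.** Target: at least 30 minutes on 5 or more days a week (Abstract, Background, Moderate physical activity), a minimum of 5 × 30 = 150 minutes a week. Item: 30 minutes, with both a daily and a 3-to-5-times-weekly frequency (Other assessments). Weekly minutes = days × 30. Share of the minimum = weekly minutes / 150.

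**Readings.** A: 3 to 5 times is a floor of 3. B: 3 to 5 times is a literal range. C: the daily wording governs.

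| Days/week | Minutes (share of 150) | Target met | A | B | C |
|---|---|---|---|---|---|
| 0–2 | 0–60 (0–40%) | no | no | no | no |
| 3 | 90 (60%) | no | **yes** | **yes** | no |
| 4 | 120 (80%) | no | **yes** | **yes** | no |
| 5 | 150 (100%) | yes | yes | yes | **no** |
| 6 | 180 (120%) | yes | yes | **does not fit** | **no** |
| 7 | 210 (140%) | yes | yes | **does not fit** | yes |

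Bold cells disagree with the target column.

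- Reading A misplaces men at 3 and 4 days. They answer yes and become action or maintenance, depending on duration.
- Reading B makes the same error, and men at 6 and 7 days meet the target but fall outside the item's range.
- Reading C misplaces men at 5 and 6 days. They answer no and become preparation, contemplation or pre-contemplation.

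No column reproduces the target's cut-off between 4 and 5 days. Men at 0–2 days are classified consistently under all three readings. The errors lie among men at 3–6 days, plus those at 7 days under the literal range. The article does not give the distribution of walking frequency, so the number affected among the 47 + 47 = 94 men cannot be computed.

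The fruit and vegetable part of the same question uses the same five-a-day threshold as the dietary target. Matching an item to its target was therefore feasible within this instrument.

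**The case against.** The strongest reply has four parts.

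**Loose wording.** The daily phrase may simply mean minutes per session, as in the minimum asked of each patient under Moderate physical activity. That is plausible, and it would remove both the internal contradiction and the misstaging of men at 5 or 6 days. It leaves the gap between a threshold of 3 and a threshold of 5.

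**Little effect on delivery.** A reader might infer that men below target who are staged as maintenance miss the walking intervention. The document does not support this. Every intervention patient is asked for the 5-day minimum whatever his stage. The walking component is tailored on baseline activity, and pedometers, weekly step goals, regular calls and a 3-month adherence check apply as well. What could be lost is the extra emphasis described for contemplators and pre-contemplators. This part of the objection largely stands.

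**Little effect on the analysis.** A reader might also infer that the treatment comparison is compromised. It is not. Stage is not among the listed primary or secondary outcomes, the Statistics section names only baseline scores as ANCOVA covariates, and no subgroup or interaction by stage is specified. This stands for the primary comparison. It does not rescue the staging objective or the announced use of stage in interpretation.

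**No duty to mirror the target.** The companion item on avoiding too much fat does not state the numerical fat target, and the questionnaire itself is not shown. But an item without a number differs from one that states a conflicting number. The article prints this wording as what patients are asked and attaches the staging rule to it. If the questionnaire in use reads differently, the article needs correcting instead.

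**Conclusion.** The point holds as a measurement defect in a baseline instrument. The walking item is ambiguous, and under none of its readings does it match the threshold that the article gives consistently elsewhere. Men at 3 or 4 days a week (60% or 80% of the weekly minimum) can be staged as action or maintenance. If the daily wording governs, men at 5 or 6 days can be staged as preparation or lower.

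It would go too far to say that men below target are in fact staged as maintenance: the direction of error depends on how each man reads the question. The percentages are shares of walking minutes, not effects on any trial result.

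The consequence is confined to the walking part of the staging objective and to any interpretation of the effect by walking stage. The primary comparison is unaffected and the effect on delivery is small. The conclusion assumes that the printed wording is what patients answer. No view is taken on which walking frequency is right, only that the passages must be reconciled.

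**What to change.** 1. Reconcile the walking item under Other assessments with the Abstract, the Background and Moderate physical activity, so that the item's criterion is the trial's own stated target, expressed as a single frequency.
2. Add a variable recording which version of the item each enrolled man answered.
3. For men staged with the present wording, compare the walking stage with the baseline 7-Day Physical Activity Recall, as a partial check of current activity only. The recall covers seven days by intensity, with a question on how typical the week was of the previous three months. It does not isolate brisk walking and cannot confirm the six-month split between action and maintenance. Interpret these men's walking stages cautiously and say so in the report.

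The cost is one questionnaire line and one data field, with no change to treatment or to the primary analysis. The small downside is two versions of a baseline item in a trial of 94 men, which the version flag makes visible.

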### Quality control

Following the initial visit, patients are contacted by phone every 2 weeks for the first 3 months and every 3 weeks thereafter to monitor progress and compliance with the intervention and to record any possible adverse events. The control group is also contacted every 6 weeks, for a general discussion about their condition. To standardise the follow-up call a written check-list has been used and relevant information (walking steps from the previous week and their goal for the current week, illness etc.) are collected. Each participant is encouraged to bring their partner or care-giver on the day of data collection and to be present for the nutritionist's visit at their home to help to answer questions regarding dietary intake and food preparation for those who may not be actively involved in food shopping and cooking. It is also hoped that by involving the patient's partner/care-giver, the patient is encouraged to comply with the intervention at home. The baseline and follow-up (3 month and 6 month) body composition measurements are completed by the same person to avoid inter-interviewer bias. However, this person is not masked to treatment assignment. Although it is preferable to have any subjective measurements, such as body composition measurements, taken by a person who is masked to treatment allocation, this was not possible in the present study and in order to minimise any bias that may be introduced, all body measurements are taken and recorded without referring to the previously recorded measurements.

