### Recruitment of patients

Hospital notes are initially checked to identify eligible patients. The patient's consultant confirms their eligibility in terms of clinical conditions related with mobility. The study objectives, hypotheses, design and data collection procedures are then discussed with patients who meet the inclusion criteria. They are given an information sheet to read at home and are then phoned within 3-5 days to get their verbal consent to participate in the study. An appointment date is arranged for collection of baseline data at the clinic. Prior to the visit, a set of self-administered questionnaires are mailed to the patient for completion and they are asked to bring the completed questionnaires to their next visit. Patients provide written consent on the day of recruitment; before data collection. Midterm and final assessment dates are then scheduled for a 3 month (13 weeks) and 6 month (25 weeks) follow-up visit (Figure 1).

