### Data collection

Data to evaluate the efficacy of the intervention are collected at baseline and at 3 and 6 months after the intervention has begun in the intervention and control group. Data are collected via interview, self administrated questionnaire, physical and biological measurements. Data collection instruments and the study timeline are summarised in Table 1. All instruments used have been previously validated and we also pre-tested them in the Northern Irish population prior to use in the study.

**Table 1 T1:** Data collection instruments at different assessment points

	Baseline	3-month follow-up	6-month follow-up
Anthropometry	**X**	**X**	**X**

FSS	**X**	**X**	**X**

FACT-P	**X**	**X**	**X**

7-DPARQ	**X**	**X**	**X**

6-min Walk Test	**X**	**X**	**X**

PSS-10	**X**	**X**	**X**

7DD	**X**	**X**	**X**

Fasting blood sample	**X**	**X**	**X**

TTM	**X**		

Questionnaire for background information	**X**		

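### Adverse events are collected by telephone, but the intervention arm is scheduled for about 10 calls and the control arm for about 4, with a different stated purpose, so event counts by arm cannot be compared without risk of bias

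*Protocol article*

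**What the plan says.** Four places in the Protocol article bear on this.

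- **Route.** Other assessments states: "Data related to adverse events are collected continuously via follow-up phone call". It names no arm and no other route.
- **Intervention calls.** Under Quality control, "patients are contacted by phone every 2 weeks for the first 3 months and every 3 weeks thereafter", and the purpose is "to monitor progress and compliance with the intervention and to record any possible adverse events". The sentence does not name an arm, but monitoring compliance with the intervention fits only the intervention arm, and the next sentence deals with controls separately.
- **Control calls.** The next sentence reads: "The control group is also contacted every 6 weeks, for a general discussion about their condition". Recording of adverse events is not repeated there.
- **Checklist.** The section goes on: "To standardise the follow-up call a written check-list has been used and relevant information" are collected. The examples are step counts, the step goal and illness. Again no arm is named.

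Both arms also attend clinic, since efficacy data are "collected at baseline and at 3 and 6 months after the intervention has begun in the intervention and control group". Table 1 lists the instruments used at those visits, and adverse events are not among them. Adverse events are not one of the three primary outcomes, nor are they named among the secondary ones: "Secondary outcomes include nutrient intake, physical activity and perceived stress". The ANCOVA under Statistics is for primary and secondary endpoints only.

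**The concern.** The only named source of adverse-event data runs at a different frequency in each arm, and its stated purpose also differs. An arm that is asked more often, and more directly, will tend to report more events even when the true rates are equal. This follows from the stated schedule, and an analysis plan cannot recover events that were never asked about.

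At stake is the safety picture of a diet and walking programme in older men on ADT. An excess of events in the intervention arm could be a real effect or a product of the extra calls. Similar counts could hide a true advantage of the intervention. The article expects its results to inform guidelines and patient management, so events reported by arm would be read as comparative. Quality control acknowledges unmasked body measurement as a source of bias and takes a step against it, but does neither for unequal questioning about events.

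**Working it through.** The article gives no number of calls and no event rate, so there is no stated figure to reproduce. The calls can be counted from the schedule.

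**Inputs.** Follow-up visits are "scheduled for a 3 month (13 weeks) and 6 month (25 weeks) follow-up visit" (Recruitment of patients). Call intervals are 2 weeks, then 3 weeks, in the intervention arm and 6 weeks in the control arm (Quality control).

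**Number of calls**

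- Intervention, first 13 weeks: 13/2 = 6.5, so 6 calls (weeks 2, 4, 6, 8, 10, 12).
- Intervention, remaining 12 weeks: 12/3 = 4 calls. They fall at weeks 15, 18, 21 and 24 if counted from the week-12 call, or 16, 19, 22 and 25 if counted from week 13.
- Intervention total: 6 + 4 = 10.
- Control: 25/6 = 4.17, so 4 calls (weeks 6, 12, 18, 24).
- Ratio: 10/4 = 2.5. By rates it is (6.5 + 4)/4.17 = 2.52. It stays at 2.5 if follow-up is taken as 24 or 26 weeks.
- By period: 6 against 2 (3 to 1) in the first 3 months, then 4 against 2 (2 to 1).

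**From calls to recorded events.** The call ratio is not the event ratio, because each call can cover the whole time since the last one. Two illustrative models follow. Both assume equal true rates and the same questions in both arms. The recall parameters are assumptions.

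*Model A: an event is reported only if it falls within a fixed window before a call.* Coverage = sum over calls of min(window, interval) / 24 weeks.

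| Window | Intervention | Control | Ratio |
|---|---|---|---|
| 2 weeks | (10 × 2)/24 = 83% | (4 × 2)/24 = 33% | 2.5 |
| 3 weeks | (6 × 2 + 4 × 3)/24 = 100% | (4 × 3)/24 = 50% | 2.0 |
| 4 weeks | 100% | (4 × 4)/24 = 67% | 1.5 |
| 6 weeks | 100% | 100% | 1.0 |

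*Model B: recall fades exponentially with half-life h.* With k = ln 2 / h, the share recalled at a call after an interval of L weeks is f(L) = (1 − exp(−kL))/(kL). Intervention = [13 f(2) + 12 f(3)]/25; control = f(6).

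| Half-life | Intervention | Control | Ratio |
|---|---|---|---|
| 2 weeks | 0.674 | 0.421 | 1.60 |
| 4 weeks | 0.814 | 0.622 | 1.31 |
| 8 weeks | 0.900 | 0.780 | 1.15 |
| 26 weeks | 0.968 | 0.924 | 1.05 |
| Perfect recall | 1.000 | 1.000 | 1.00 |

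Both models push the same way, towards more recorded events in the intervention arm. The distortion vanishes only if recall over 6 weeks is complete and the questioning is identical. If control calls do not ask about events, neither model applies and the gap is larger.

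**The case against.** The case on the other side has five parts.

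- **More calls need not mean more events.** A reader might infer from the 2.5 ratio that counts will differ, perhaps 2.5-fold, through ascertainment alone. The article does not support that. The figure of 2.5 needs an abrupt 2-week recall limit, while the article relies on longer recall elsewhere: one month for the PSS-10, and the previous three months for judging how typical the week's activity was. This objection stands, and only a possible difference can be claimed.
- **Controls may well be asked.** A reader might infer that control calls record no events. That goes too far. The sentence on the adverse-event route names no arm, the checklist sentence comes directly after the one on control calls, and illness is an item that fits both arms. But the step and goal items fit only the intervention, so the text is ambiguous. Even identical questions would leave the difference in frequency.
- **No stated analysis is affected.** This is correct, and it limits the impact to descriptive reporting by arm.
- **Silence in an article proves little.** Table 1 lists data collection instruments, so the lack of an adverse-event row does not show that events go unasked at the visits. This stands too. The point rests on the two stated schedules and purposes, not on the gap in Table 1.
- **Unequal contact is part of a supported lifestyle programme.** True, and the extra calls need not change. But their use to collect events can be separated from the comparison of events. The bias most likely runs one way, so an excess in controls would appear despite it; an intervention excess or similar counts are what become hard to read.

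**Conclusion.** The concern holds as a risk of unequal ascertainment. The schedule gives about 10 intervention calls, expressly recording adverse events, against about 4 control calls described as general discussion, and it is unclear whether the latter use the same questions. Counts by arm may differ for this reason, most likely with the intervention inflated. With equal true rates and equal questioning, the illustrative ratio of recorded events is about 1.0 to 2.5. It rests on assumed recall, and it would be larger if controls are not asked. The primary and secondary analyses are untouched. The correction is a cheap improvement to any safety report by arm.

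**What to change.** 1. Reconcile Other assessments with Quality control by stating whether control calls use the adverse-event questions.
2. Ask the same adverse-event questions, covering the same recall period, in both arms at the existing 3- and 6-month visits, at the 6-weekly control calls and at the coinciding intervention calls. If the 3-weekly calls are counted from week 12, intervention calls already fall at weeks 6, 12, 18 and 24, so the schedule should say so. At these contacts intervention patients should be asked about the full common period, whatever they reported in between.
3. Base any by-arm comparison of events on these common contacts, and list events found only at the additional intervention calls separately.

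The cost is a short set of common questions, which the existing checklist could carry, and a sentence or two of text. No new contacts or staff are needed. There are two downsides. Some intervention-arm events leave the comparison, though they are still reported. And intervention patients, being questioned more often, may remain primed to report at the common contacts, so the bias is reduced rather than removed.
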